## Discussion

3

Since chest pain and other symptoms account for about 5% to 10% of the total number of emergency patients,^[14]^ accurate diagnosis of AMI in chest pain patients in the early stage is of great clinical value in improving the prognosis of patients and reducing their mortality.

Troponin T is a regulatory protein for myocardial tissue contraction and a biochemical marker of myocardial injury and necrosis. It is usually detected from the blood 4 to 6 hours after chest pain occurs. Traditional cTnT detection methods have lower sensitivity and affect the early diagnosis of AMI, while hs-cTnT have higher sensitivity than traditional detection methods.^[15]^ Hs-cTnT has high sensitivity to myocardial injury and strong specificity, can appear in the early stage of AMI, and can exist in the blood stream for a long period of time. It is the most favorable marker for early diagnosis and prognosis evaluation of AMI.^[16]^ The hypersensitive troponin will rise abnormally when there is damage of cardiomyocytes and the sensitivity is high, serum level of hypersensitive troponin T is positively correlated with the degree of myocardial injury in acute myocardial infarction.^[17]^

Copeptin, a part of the original C-terminal of arginine vasopressin (AVP), is positively correlated with AVP in the normal population and patients with cardiopulmonary and vascular diseases, and is an acute endogenous stress marker. Its stability in vivo is stronger than AVP, and it is easy to measure. Therefore, copeptin can replace AVP as a clinical early-warning marker of cardiovascular disease.^[18]^ The plasma copeptin level peaks immediately after AMI, and decreases gradually within 6 hours, with the largest change range within 0 to 3 hours.^[19]^ However, the copeptin specificity is low, and it can increase in acute or chronic stress state, such as respiratory tract infection, chronic obstructive pulmonary disease, heart failure, critical illness and so on, which has certain influence on the early diagnosis of AMI.^[20]^ The combination of copeptin and hs-cTnT detection is expected to improve specificity and accuracy in early diagnosis of acute myocardial infarction.

Cardiac troponin I remains the preferred cardiac marker for AMI diagnosis, according to guidelines published by the European Society of Cardiology (ESC), the American College of Cardiology (ACC), and the American Heart Association (AHA).^[21,22]^ Therefore, we used cTnI as a control group to evaluate the clinical value of copeptin combined hs-cTnT in the diagnosis of early acute myocardial infarction.

This study may have the following limitations: because this is a single central regional experimental study, the inclusion of the population may be relatively single, there is a certain bias; factors such as age may have a certain impact on the results.

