**Methods::**

This is a prospective, randomized; double-blind diagnostic trial to investigate the diagnostic value of copeptin combined with hypersensitive troponin T detection in early acute myocardial infarction. Approved by the clinical research ethics of our hospital. Patients were randomly divided into one of 2 test protocols: (A) copeptin combined with hs-cTnT group and (B) cardiac troponin I (cTnI) group. Patients, doctors, nurses, inspectors, and data-gathering assistants were blinded to group allocation. We will focus on the sensitivity comparison of the 2 detection methods at different time periods and the sensitivity and specificity comparison of the two detection methods. Data were analyzed using the statistical software package SPSS version 25.0 (Chicago, IL).

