## Introduction

1

Acute myocardial infarction (AMI) is an acute coronary syndrome in which blocked coronary artery causes insufficient blood supply to the heart muscle and impairs heart function, has the characteristics of rapid progression and high mortality,^[1]^ is the leading cause of cardiovascular death worldwide.^[2]^ Rapid and accurate early diagnosis of AMI is the key to reduce mortality and improve prognosis of patients.^[3]^

In the previous clinical diagnosis, AMI was mainly diagnosed based on medical history, physical examination, electrocardiogram, echocardiography and other examinations, but all of these examinations had certain defects and their accuracy was not high, while myocardial necrosis markers such as C reactive protein (CRP), myoglobin (Mb), creatine kinase isoenzyme (CK-MB) have poor sensitivity and specificity in the early stage of the disease.^[4]^ Although cardiac troponin (cTn) has become a recognized indicator for the diagnosis of AMI, the blood concentration reflecting myocardial necrosis cannot be detected within 1 hour after the onset of AMI symptoms, and the level of troponin begins to rise 3 to 6 hours after the occurrence of myocardial injury, appearing the “troponin blindness stage”,^[5]^ since cTn lacks sensitivity in the early stages of myocardial injury, it is particularly important to add a marker for rapid diagnostic AMI. Copeptin is a newly discovered marker of myocardial necrosis. Clinical studies have confirmed that copeptin begin to rise in early AMI, earlier than troponin,^[6]^ breaking the “troponin blindness stage” and making up for defects in early atypical changes in electrocardiogram. Early diagnosis and prognosis evaluation of AMI can be carried out quickly.

Some studies have pointed out that although the level of copeptin in AMI patients is significantly increased, because of the lack of specificity, it should not be considered as a single biomarker for the diagnosis of suspected AMI patients.^[7]^ The sensitivity of hypersensitive cardiac troponin (hs-cTn) is higher than that of traditional troponin. At present, the diagnostic value of hs-cTn combined with copeptin in early detection of AMI is not clear. The aim of this study is to investigate the early diagnostic value of hs-cTnT combined with copeptin in early detection of AMI.

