### Sample size

2.3

Estimation of sample contents for both test and control groups will be obtained based on anticipated sensitivity according to Buderer formula:^[9,10]^$$n=\frac{Z_{1-\frac{a}{2}}^{2}\times S_{N}\times \left(1-S_{N}\right)}{L^{2}\times Prevalence}$$

Where n = required sample size; S_N_ = anticipated sensitivity; *α* = size of the critical region (1 – α is the confidence level); Z_1-α/2_ = standard normal deviate corresponding to the specified size of the critical region (α), and L = absolute precision desired on either side (half-width of the confidence interval) of sensitivity or specificity. According to the sensitivity of the test group to be 90% and that of the control group to be 75%, the sensitivity of the control group to be 0.8, α=0.05, Z_1-α/2_ = 1.96, L = 0.1, it is calculated that at least 43 persons are required to be included on the test group and 90 persons on the control group. At last, 90 persons are selected from the test group and the control group respectively.

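### The only planned comparison changes the troponin assay and adds copeptin at the same time, so it measures the package and cannot identify what copeptin adds

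*Protocol article*

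**What the plan says.** The Abstract (Methods) and section 2.5 define two arms: "A) copeptin combined with hs-cTnT group and (B) cardiac troponin I (cTnI) group". Section 2.8 compares the areas under two ROC curves by a Z test, and the Abstract names sensitivity and specificity of the two methods as the focus. The Discussion explains the comparator: troponin I is the marker that guidelines prefer, and so "we used cTnI as a control group to evaluate the clinical value of copeptin combined hs-cTnT".

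The aim is worded for the combination: "The aim of this study is to investigate the early diagnostic value of hs-cTnT combined with copeptin in early detection of AMI". The rationale in the Introduction is about adding something to troponin: "since cTn lacks sensitivity in the early stages of myocardial injury, it is particularly important to add a marker for rapid diagnostic AMI". The document also says, before any copeptin is considered, that "The sensitivity of hypersensitive cardiac troponin (hs-cTn) is higher than that of traditional troponin", and the Discussion repeats the point for the T assay ("while hs-cTnT have higher sensitivity than traditional detection methods").

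Section 2.3 plans on sensitivities of 90% in the test group and 75% in the control group. Section 2.6 describes hs-cTnT and copeptin as separate assays, each with its own cut-off, on plasma taken at 0, 4 and 6 hours.

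**The concern.** Two things change between the arms, and the protocol expects one of them, the newer troponin assay, to raise sensitivity by itself. On the protocol's own premises the test arm should beat cTnI even if copeptin contributes nothing. A positive result would support the package against cTnI. It would not show that adding copeptin to a high-sensitivity troponin helps.

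Specificity raises the same problem. The Discussion concedes that copeptin has low specificity, yet expects the combination to improve it. A contrast with cTnI cannot show whether copeptin costs specificity relative to hs-cTnT alone. The limitations paragraph mentions the single centre and factors such as age, but not this.

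**Working it through.** **Inputs.** From section 2.3: anticipated sensitivities 0.90 and 0.75, Z = 1.96, L = 0.1, a value of 0.8, and 90 patients per arm. The sensitivity of hs-cTnT alone is not given, so a range is assumed. The lower end, 0.75, is the control value; the document says hs-cTn is above traditional troponin. The upper end, 0.90, is the combination's value; under an either-positive rule one component cannot exceed the combination. That rule is also an assumption, because the article states no combination rule.

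**The plan's own figure.** Buderer: n = 1.96² × Sn × (1 − Sn) / (L² × prevalence).
- Test: 3.8416 × 0.90 × 0.10 / (0.01 × 0.8) = 43.2
- Control: 3.8416 × 0.75 × 0.25 / (0.01 × 0.8) = 90.04

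The stated 43 and 90 are reproduced when 0.8 is used as the prevalence, although the text labels it a control-group sensitivity. With prevalence 1 the results are 34.6 and 72.0, which do not match. This matters here only for the number of AMI patients in the test group: 90 × 0.8 = 72 on the prevalence reading, or 90 if everyone enrolled has AMI, as section 2.4 implies.

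**Splitting the planned gain.** Total = 0.90 − 0.75 = 15 points. With h the assumed sensitivity of hs-cTnT alone, the assay contributes h − 0.75 and copeptin d = 0.90 − h.

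| h (assumed) | From assay | From copeptin (d) | Power, separate arms of 90 | Power, paired, 90 AMI | Power, paired, 72 AMI |
|---|---|---|---|---|---|
| 0.75 | 0 | 15 | – | – | – |
| 0.80 | 5 | 10 | 47% | 90% | 74% |
| 0.825 | 7.5 | 7.5 | 31% | 68% | 46% |
| 0.85 | 10 | 5 | 17% | 29% | 15% |
| 0.875 | 12.5 | 2.5 | 8% | 3% | 1% |
| 0.90 | 15 | 0 | – | – | – |

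Every row gives the same 90% versus 75% in the planned comparison, which therefore cannot tell them apart.

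The power columns concern the combination against hs-cTnT alone. Separate arms: two-sided pooled test of two proportions at 0.05, counting 90 AMI patients per arm. Paired: under the either-positive rule all discordant pairs go one way, so their number is binomial (N, d). Exact McNemar needs at least 6 such pairs (2 × 0.5⁶ = 0.031; 5 pairs give 0.0625), and power is P(B ≥ 6).

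**Precision of the paired increment.** Half-width = 1.96 × √(d(1 − d)/N).
- d = 0.05: 1.96 × √(0.0475/72) = 5.0 points; with N = 90, 4.5 points
- d = 0.10: 1.96 × √(0.09/72) = 6.9 points; with N = 90, 6.2 points

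At d = 0.05 only 72 × 0.05 = 3.6 to 90 × 0.05 = 4.5 discordant pairs are expected, so the normal approximation is rough there.

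**Specificity.** On the 80% reading there are 90 − 72 = 18 non-AMI patients per arm. A 10-point one-directional loss then has a half-width of 1.96 × √(0.09/18) = 13.9 points. If section 2.4 is applied as written, there may be no non-AMI patients at all.

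**The case against.** The strongest reply is that the trial asks a package question and answers it. Every statement of the aim concerns the combination, and a new strategy against the guideline-preferred marker is a legitimate comparison. This stands. A reader might infer that the stated question goes unanswered; the documents do not support that, because only copeptin's increment is left open.

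A reader might also infer that any gain will be credited to copeptin. No text says so. The sentence on adding a marker is background, and the Abstract's Discussion speaks of evidence for hs-cTnT detection. The package contrast cannot isolate that component either, but it is not a claim for copeptin.

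A third reply is that a within-arm analysis may sit in a full protocol or analysis plan that is not shown. That is possible, so its absence from the article is not itself the fault. The point rests on what the article fixes: the two arms, the comparator with its justification, and the comparison of two ROC curves.

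Finally, the paired analysis has limits. Under an either-positive rule sensitivity cannot fall when copeptin is added, so the sensitivity comparison can only favour copeptin, and small increments will not be resolved. Both limits stand. They are reasons to report an estimate with its interval, not to omit it.

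**Conclusion.** The point holds in a limited form. The planned contrast with cTnI estimates the effect of changing the assay and adding copeptin together; it does not identify copeptin's contribution. Of the 15 planned points, that contribution could be anything from all to none over the assumed 75% to 90% range for hs-cTnT alone. No single value in that range has support in the documents.

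The conclusion that the contrast is confounded needs no assumed number. The split rests on the assumed range, and the precision and power figures also on the either-positive rule and on 72 to 90 AMI patients in the test group. The trial's package question is not invalidated. The amendment is worth making because it extends what the trial can conclude without new data.

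**What to change.** In section 2.8:

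- Add a secondary paired analysis within the test group: the combination against hs-cTnT alone, same patients, 0-hour sample. State the combination rule beforehand and report the paired difference in sensitivity with a 95% confidence interval.
- Report paired specificity and AUC differences only if non-AMI patients are enrolled. Under an either-positive rule the cost of copeptin appears only in specificity, so without such patients say that this cost is not assessed.
- Describe the contrast with cTnI as the effect of the whole package, and base any statement about copeptin on the paired estimate.
- State in advance that increments of about 5 points or less will probably be inconclusive at this sample size.

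The cost is analysis text and a sentence in the limitations. Both assays are already planned in the test group, so no extra arm, patient or sample is needed.

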### Randomization and blinding

2.5

Patients were randomly divided into one of 2 test protocols:

1.Copeptin combined with hs-cTnT group,2.cTnI group.

Randomization was performed without any stratification. Randomization listings were prepared with a probability of 1:1 and after that, randomized numbers were printed according to the results of the randomization. After the patient had given consent, the members of the inpatient clinical research center divided the patients into 2 groups according to the parity of the assigned numbers, the odd number was the test group, and the even number was the control group. Patients, doctors, inspectors, nurses and research assistants collecting data were blinded to group allocation.

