### Statistical analysis

2.8

SPSS 25.0 was used for statistical analysis of the data and normality test of the measurement data. The normal distribution data were expressed as $\bar{x}\pm S$, and the comparison between groups was performed by one-way ANOVA. Non-normal distribution data were represented by median and quartile, rank sum test was used for comparison between groups, Chi-Squared test was used for comparison between count data sets. Receiver operating characteristic curve (ROC) was used to screen the best diagnostic critical point value, and its sensitivity and specificity were calculated to evaluate the diagnostic effect. The area under the 2 ROC curves (AUC) was compared by *Z* test. *P* < .05 was statistically significant.

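### The arms hold different patients and only unadjusted comparisons are named, so a small, cheap gain in precision from adjusting for age and time from onset is given up

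*Protocol article*

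**What the plan says.** Section 2.5 of the protocol article assigns each patient to copeptin plus hs-cTnT or to cTnI. It says "Randomization listings were prepared with a probability of 1:1" and "Randomization was performed without any stratification". The two sensitivities therefore come from different people.

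The abstract sets the aim: "We will focus on the sensitivity comparison of the 2 detection methods at different time periods". For analysis, section 2.8 says "Chi-Squared test was used for comparison between count data sets" and "The area under the 2 ROC curves (AUC) was compared by *Z* test". It names no covariate and no regression model, and it does not rule them out. It does not expressly tie chi-squared to sensitivity, though that is the natural reading for a comparison of proportions.

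The limitations at the end of section 3 say "factors such as age may have a certain impact on the results". Time from onset is not named there, but it runs through the text:

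- Section 2.4 admits patients who reach hospital up to 2 hours after chest pain starts.
- Section 2.6 takes blood at 0, 4 and 6 hours after admission.
- Section 1 says troponin is undetectable in the first hour and starts to rise at 3 to 6 hours.
- Section 3 says troponin T is usually found 4 to 6 hours after chest pain, and that copeptin changes most over the first 3 hours.

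**The concern.** When two tests are read on different patients, a chance difference between the arms in anything that drives positivity becomes part of the observed sensitivity difference. The article itself offers two such factors.

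Age is named outright. Time from onset follows from the sampling scheme: samples with the same nominal time can differ by up to about 2 hours from onset. The admission sample falls 0 to 2 hours after onset, across the first hour in which troponin is undetectable and within the period of fastest copeptin change. The 4-hour sample falls 4 to 6 hours after onset, across the window given for troponin T.

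Adjusting for baseline predictors removes this component of random error. At stake is some precision in the main comparison, whose power for the planned sensitivities is not generous.

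**Working it through.** **Inputs.** From section 2.3: "According to the sensitivity of the test group to be 90% and that of the control group to be 75"% (so 0.90 and 0.75), Z = 1.96, L = 0.1, a value of 0.8, and 90 patients per arm. The strength of the age effect is not in the documents. It is varied as an assumed odds ratio (OR) per SD of age.

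**1. The plan's own figures.** Buderer's formula with 0.8 as prevalence:

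- test arm: 1.96² × 0.90 × 0.10 / (0.1² × 0.8) = 43.2
- control arm: 1.96² × 0.75 × 0.25 / (0.1² × 0.8) = 90.04

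These match the stated 43 and 90. Section 2.3 labels the 0.8 as a control-group sensitivity, but the figures reproduce only if it is the prevalence. On that reading an arm of 90 holds 0.8 × 90 = 72 AMI patients. Section 2.4 admits only patients who meet AMI criteria, which points to 90. Both are used below.

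**2. Unadjusted precision and power.** The SE of the difference at 90 per arm is √[(0.09 + 0.1875)/90] = 0.0555, so the 95% half-width is 10.9 points. With pooled proportion 0.825, power is Φ{[0.15 − 1.96 × √(2 × 0.825 × 0.175/90)] / 0.0555} = Φ(0.70) = 76%. At 72 per arm the same steps give 66%.

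**3. Adjusting for age alone.** Simulation, 6,000 trials per row; logistic model with arm and age, likelihood-ratio test, and the standardised difference in sensitivity.

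| AMI patients per arm | OR per SD of age | Power, chi-squared | Power, adjusted | Variance ratio |
|---|---|---|---|---|
| 90 | 1.0 | 77.3% | 78.6% | 1.00 |
| 90 | 1.5 | 76.7% | 78.4% | 0.99 |
| 90 | 2.0 | 76.5% | 79.6% | 0.95 |
| 90 | 3.0 | 77.5% | 84.5% | 0.86 |
| 72 | 1.0 | 67.9% | 68.0% | 1.01 |
| 72 | 1.5 | 67.9% | 69.0% | 0.98 |
| 72 | 2.0 | 67.2% | 70.7% | 0.94 |
| 72 | 3.0 | 67.4% | 74.2% | 0.89 |

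At OR 1.0 age carries no information. The rise of about 1 point at 90 per arm therefore reflects the change of test statistic and simulation error (about √(0.77 × 0.23/6000) = 0.5 points per power estimate). Gains of 1 to 2 points should be read in that light.

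**4. Adjusting for age and onset time together.** A separate simulation at the same sensitivities, with 72 or 90 per arm, gave variance reductions of 0% (weak predictors), 3 to 6% (moderate) and 12 to 14% (strong). Power rose by about 1 to 7 points.

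**5. What chance imbalance is worth.** The difference in mean age has SD √(2/90) = 0.149 SD units, a 95% range of ±0.29. In points of sensitivity, the share of error that adjustment removes at 90 per arm has SD √(0.0553² − 0.0538²) = 0.013 at OR 2 and √(0.0553² − 0.0513²) = 0.021 at OR 3. The 95% ranges are about ±2.5 and ±4.0 points.

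**6. Validity of the unadjusted test.** With equal sensitivities of 0.75 and 90 per arm, its type I error was 5.3%, 4.9% and 5.3% at OR 1, 2 and 3.

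**7. Sparse false negatives.** At the planned sensitivities an arm of 90 expects 9 misses (test) and 22.5 (control). If sensitivity were higher at later samples, say 98% against 93% (assumed), the test arm would have no misses at all with probability 0.98⁹⁰ = 16%, and the arm coefficient would then not be estimable by ordinary logistic regression.

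**The case against.** The strongest case against is that nothing here is wrong. Unstratified 1:1 randomisation followed by an unadjusted test is a legitimate design. Only a condensed article is at hand, and covariate adjustment is often settled in an analysis plan that is not shown. This stands to the extent that the absence of adjustment cannot be called a defect. What remains is a better choice for a method that section 2.8 does name.

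A reader might infer that the sensitivity comparison is biased, or that the lack of stratification makes it unreliable. The documents do not support that. Chance imbalance is already covered by the standard error, and the type I error in step 6 stays near 5% even with a strong age effect.

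Three further points stand in part:

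- The remark on age follows one about a narrow single-centre population, so it may concern generalisability, which adjustment between arms would not address. The argument from onset time does not depend on it.
- Eligibility requires knowing that arrival was within 2 hours. The article does not say that the time itself is recorded, so the covariate cannot be assumed to be available.
- A logistic model changes the estimand to a conditional odds ratio unless results are standardised, and it can fail where misses are few.

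**Conclusion.** The point holds as a minor improvement. The planned unadjusted comparison is valid; it gives up a little precision that baseline information could recover. Variance would fall by about 0 to 6% with weak to moderate predictors and by up to about 14% with strong ones, and power would rise by about 1 to 7 points from a base of roughly 66% (72 AMI patients per arm) to 76% (90 per arm). With weak predictors the gain is practically nil, but precision is not materially worsened.

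These figures rest on sensitivities of 90% and 75% from section 2.3, on 72 or 90 AMI patients per arm, and on predictor strengths that are assumed throughout. They apply to the sensitivity comparison, on the reading that chi-squared is meant for it. The Z test on the AUCs would need its own covariate method.

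**What to change.** In section 2.8, prespecify for patients with AMI a logistic regression of test positivity on arm, age and time from onset. Report the standardised difference in sensitivity with a 95% confidence interval (delta method or bootstrap), and keep the chi-squared test as the supporting analysis. State in advance that at sampling times with very few false negatives the analysis falls back to the unadjusted comparison or to a penalised (Firth) fit. Record time from onset as a value when the 2-hour criterion is checked.

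The cost is a few sentences, one recorded data item and some extra analysis work. No additional patients are needed.
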